**Fig 1 pone.0272481.g001:**
[figure not shown]
Potential mechanisms and pathways through which Bolsa Familia Program (BFP) may affect mental health-related hospitalizations and suicide among children and youth.

Therefore, the main potential mechanisms this project will test, through which BFP may be associated with better mental health outcomes are: (i) by reducing parental mental illnesses and family separations; (ii) by improving school retention (BFP has conditionalities related to education and health); (iii) by reducing exposure to violence; and finally, (iv) by decreasing impulsivity (Fig 1).

This protocol offers a unique opportunity to test these mechanisms in a countrywide dataset, and allows subgroup analyses. Considering that the impact of those factors may happen differently among more vulnerable groups, such as black youth, women, youth with lower income and living in deprived areas, after examining the impact of cash transfers on interrupting the pathways between poverty and poor mental health through one or more mechanisms previously mentioned (e.g., improving educational outcomes, reducing impulsivity, etc). We will then evaluate the differential impact of BFP across race and gender, and how this might be explained by the mechanisms. If the effect of the cash transfer is stronger among minorities, decreasing inequalities, it can also be one of the mechanisms through which this program may improve youth mental health.

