#### Data and measures

Datasets, variables, and sample sizes.

***100 Million Brazilian Cohort*.** We will analyze a cohort of subjects registered in Unified Registry for Social Programs (CadÚnico). The CadÚnico is a data collection and storage system that contains individual records with demographic and socioeconomic information on the poorer half of the Brazilian population (n = 114,007,705). Anyone who meets the eligibility criteria can be registered by visiting one of the Centers for Social Assistance (CRAS) or be registered at home, as social workers visit households periodically to identify and register eligible individuals. The criteria to be eligible for CadÚnico registration are: having a monthly family income per capita of half the minimum salary in Brazil (778 reals in 2015) or less; or having a total family income (monthly) of up to three minimum salaries. The CadÚnico contains information about housing conditions, income and demographic characteristics of all the members of a registered family [26].

***Bolsa Familia Program (BFP)*.** The Brazilian Cash Transfer Program (BFP) is the largest poverty alleviation program in the world, with about 46 million people having received the benefit up to 2015. It has three aims: income supplement guarantee for immediate relief of extreme poverty (people who live with up to 70 reals per capita) [27]; access to public services (improving education, health, and citizenship of families); and productive inclusion to increase the capacity and job opportunities, and income generation among the poorest families [28].

In 2014, the eligibility criteria for participation in the program (which is more stringent than the conditions for eligibility to register in CadÚnico) was having an income of less than 77 reals (14 USD) monthly per person or less than 154 reals in cases where there is a child, adolescent or pregnant woman in the family. The benefits were: “basic benefit”, 77 reals monthly, regardless of family composition; an extra 35 reals to families with a child or adolescent between 0–15 years, or a pregnant or nursing woman; and an extra 42 reals per adolescent from 16–17 years, in 2014. Families living in extreme poverty can accumulate all these “basic benefits” to a maximum of 1,332 reals per month (235 USD).

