**Fig 2 pone.0272481.g002:**
[figure not shown]
Flowchart of non-beneficiary (non-BFP) and beneficiary of the Bolsa Familia Program (BFP) to test the association between BFP and youth mental health-related hospitalizations and suicide.

**Table 1 pone.0272481.t001:** Summary of the dataset’s description, from 2001 to 2018.

Dataset	Description	Sample	Variables of interest
The 100 Million Brazilian Cohort Baseline^70,73^	It was built from socioeconomic and demographic information of individuals applying for social benefits in Cadastro Unico (CadÚnico). CadÚnico is an extensive questionnaire with information on the household and on each individual.	114 million Brazilian cohort, including 66,079,181 Bolsa Familia Program beneficiaries and 47,928,524 non-beneficiaries. Among them 41,764,126, youth aged from 5–24 years old in the day of registration.	Demographic and socioeconomic variables (sex, age, ethnicity, education, work), conditions of the household (type of residence, material of household, household density, household supply, garbage destination etc), Health Care utilization, Institutional and community support (participation in groups, access to Social Assistance Reference Center, etc.) and Brazilian government social protection programs (BFP, etc).
Mortality Information System (SIM)^74,75,72^	The national system aimed to collect information on all deaths in Brazil death certificates. All deaths are recorded using a national standardized form and causes of death are registered according to the updated International Classification of Diseases CID-10.	All mortality cause (n = 21,313,290), including suicide (n = 181,527).	Demographic and socioeconomic variables (sex, age, ethnicity, education, work), place the death took place and primary and secondaries causes of death.
Hospital Information System (SIHSUS)^1^	All hospitalizations admissions financed by the Brazilian National Health System are recorded in this system. It includes about 80% of the Brazilian populations, approximately 150 million people	Hospitalizations from mental illness 5,478,980, including: 1,698,663 from alcohol and substance use-related disorders; 1,952,605 from schizophrenia; 832,974 due mood disorders, etc.	Identification and qualification of the patient, procedures, examinations, and medical acts performed, diagnosis, reasons for discharge, amounts due etc.

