To evaluate the impact of the countrywide cash transfer program on those outcomes, we will run Regression Discontinuity Design (RDD), Propensity Score Matching (PSM), and difference-in-differences, which are robust methods of impact evaluation in public health. This should help to identify the best statistical techniques to evaluate the impact of BFP on mental health-related hospitalization and suicide. Different evaluation methods make different assumptions. For instance, PSM assumes that after matching for the observed characteristics, there is no unmeasured confounding for the association between the intervention and the outcome. RDD instead assumes that people just below and just above the threshold of a continuous variable used as eligibility criteria for the intervention are “similar” in all relevant respects. Therefore, the difference in the outcome between the intervention groups is practically random near the threshold. PSM is a method that has been used in large electronic health records [10, 32]. It allows for matching where a true case-control design was not possible, which is usually the case for electronic health records of the type we will use in this project. A propensity score is a scalar summary of measured characteristics prior to treatment (potential confounders). Therefore, treated, and untreated subjects with equivalent propensity scores, also present similar pre-treatment characteristics. This method permits the generation of a grouping between intervention and no intervention that mimics the state of randomization. In our study, people who were part of one of the aforementioned programs would have specific characteristics, to control for that we will find a match for them on the remaining dataset (114 million) considering their age, sex, educational level, income, location of residence (urban/rural), household living conditions including household density, water supply, sewage and garbage collection, previous psychiatric hospitalization, residency type and building material. This allows us to inspect whether these subjects are at a higher or lesser risk of developing mental illness later in their lives. We assume that if the PSM models’ findings are similar to RDD, the results are robust given the underlying assumptions of each different model.

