**Aim 2: To test four mechanisms and pathways of the social-economic intervention on reducing mental illness among youth; and Aim 3: To evaluate whether equity was a moderator of the effectiveness of the cash transfer program**, **e.g., whether the Brazilian cash transfer program improved the lives of most vulnerable subgroups (with lower income, black population, and women) compared to less vulnerable groups reducing mental health disparities.**

We will evaluate whether BFP program affects youth mental health through improving social drivers by running Regression Discontinuity Design (RDD) and Propensity Score Matching (PSM), and Structural Equation Modelling (SEM) for each of them and the outcomes. Such strategies allow us to examine the pathways by testing the impact of the intervention on variables that might be on the pathway of the relation between BFP and mental health outcomes. We hypothesize that BFP has an effect on reducing mental health-related hospitalizations and suicide among youth because it also affects their social drivers. Stratified analyses by municipality size, regions, states, and levels of Human Development Index (HDI) will also be performed.

We will include a set of covariates recognized as social drivers of mental illness for youth at the individual level such as income, income instability, unemployment, isolation and at the contextual level, variables from the municipalities where the youth live, such as population, fertility, mortality, migration, housing characteristics, characteristics of the neighbourhood, municipal income, labour, economic inequality (Gini index), Human Development Index (HDI), proportion of poor people and municipal coverage of the community mental health center and number of mental health professionals in the same municipality. We will also evaluate whether equity was a moderator of the effectiveness of the cash transfer program, e.g., whether the Brazilian cash transfer program improved the lives of most vulnerable subgroups compared to less vulnerable groups, thereby reducing mental health disparities. Therefore, we will repeat the analysis stratifying by subgroups with diverse ranges of income level, black compared with the white population, and female compared to male.

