Some limitations must be considered. The use of proxy in one of the four mechanisms proposed, physical injuries for impulsivity, can be a possible limitation in the analysis of mechanisms. However, assessment of impulsiveness and aggression in studies of risk factors for suicidal behavior, often depend on information from proxy informants, have been evaluated as robust [42]. Since both will be controlled by health care access, it is unlikely to have major differences between the group exposed and non-exposed. Quality of administrative data could also be challenging in these studies. Problems with quality can be related to problems with data collection and completeness of the data. However, most of the variables chosen for this project have less than 1% missing data. Most data that will be used for this proposal comes from CadÚnico that tend to be filled with precision due to the legal consequences on the beneficiaries. The forms are filled by trained interviewers, and missing information could result in not participating in the cash transfer program.

The large-scale data set will allow us to investigate comprehensively and in subpopulations the effects of BFP on youth mental health, as well test mechanisms of this effect. The use of these databases will allow exploring mental health outcomes with a high level of statistical power. The databases used in this study have national coverage, low under-registration, and some have already documented reliability. Therefore, this study will provide a comprehensive and representative analysis of the poor and extremely poor Brazilian population and reinforce the adequacy of these bases for epidemiological investigations. Results from this innovative project are expected to inform national efforts to prevent mental illnesses among youth from low-income communities in Brazil through the scale-up of economic interventions; our findings may also be relevant to other comparable middle income countries experiencing challenges, such as those resulting from the economic consequences of the COVID-19 pandemic, to address the burden of mental health problems among youth and reducing mental health disparities.

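### Control for health care access, as the protocol describes it, does not support the reassurance about injury admissions as a proxy for impulsivity

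*Protocol article*

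**What the plan says.** **The reassurance.** In the limitations paragraph of the Discussion, the protocol concedes that using physical injuries to stand for impulsivity may be a weakness. It then answers: "Since both will be controlled by health care access, it is unlikely to have major differences between the group exposed and non-exposed". The Conceptual framework confirms that the proxy is hospitalization for injury.

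**The BFP match.** Under Analytic strategy, Aim 1, matches are sought "considering their age, sex, educational level, income, location of residence (urban/rural), household living conditions", and the list goes on with "household density, water supply, sewage and garbage collection, previous psychiatric hospitalization, residency type and building material".

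**Other mentions of access.** The Aim 1 hierarchical regressions on social drivers are adjusted for access to mental health care, with no level or measure given. For Aims 2 and 3, the contextual covariates end with "municipal coverage of the community mental health center and number of mental health professionals in the same municipality". Table 1 lists, among the cohort baseline variables, "Health Care utilization, Institutional and community support"; no model names the utilization variable.

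**BFP and access.** Data and measures gives as a program aim "access to public services (improving education, health, and citizenship of families". The Conceptual framework notes that "BFP has conditionalities related to education and health". The opening of the Discussion expects BFP to ease difficulties in reaching health services, among others.

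**The concern.** An injury or psychiatric admission requires two things: the event or illness, and being admitted for it. If beneficiaries and non-beneficiaries differ in the second, a difference in admissions is not a clean measure of the first. The protocol says control for access makes a major difference unlikely, so it matters whether the described models contain that control and whether such control could work.

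At stake are the impulsivity mechanism in Aim 2 and outcomes A to H in Aim 1, which are all listed as hospitalizations, wherever they are read as illness or behaviour. A real reduction could be masked or appear as harm if BFP raises admission, or be exaggerated if better outpatient contact lowers it.

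**Working it through.** The protocol gives no figure on this point, so there is none to reproduce. The check sets its statements side by side and then illustrates the mechanism on assumed values.

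**Step 1. Is access in the BFP contrast?**

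| Analysis | Access variable named | Level and measure |
|---|---|---|
| Matching for BFP (Aim 1) | None; nearest is previous psychiatric hospitalization | Individual; reflects past use or severity, not access to injury care |
| Hierarchical regressions on social drivers (Aim 1) | Access to mental health care | Not stated |
| Covariates for Aims 2 and 3 | Mental health center coverage; number of mental health professionals | Municipal |
| Cohort baseline (Table 1) | Health care utilization | Individual or household questionnaire; not assigned to any model |

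The individual covariates given as examples for Aims 2 and 3 (income, income instability, unemployment, isolation) include no access measure.

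**Step 2. Could the measured covariates do the job?** A municipal supply variable has the same value for a beneficiary and a non-beneficiary in the same municipality at the same time. It cannot remove a difference between them there. Both named supply variables concern mental health care, while the sentence defends admissions for physical injury.

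**Step 3. When does the difference arise?** If BFP improves access, as the protocol expects, the resulting difference in admission follows exposure.

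- Baseline matching and area covariates do not remove it.
- Regression discontinuity does not either, because the change in access comes with the program at the income threshold.
- Agreement between matching and discontinuity, which Aim 1 takes as a sign of robustness, would not reveal it, since both carry it.
- A measure of access taken after enrolment would condition on a consequence of BFP.

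**Step 4. Illustration.** Observed admission ratio = true illness (or injury) ratio × ratio of the probability of admission given illness, BFP to non-BFP. All inputs are assumed.

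| True illness ratio | Admission ratio given illness | Observed ratio |
|---|---|---|
| 0.90 | 1.00 | 0.90 × 1.00 = 0.90 |
| 0.90 | 1.05 | 0.90 × 1.05 = 0.945 |
| 0.90 | 1.10 | 0.90 × 1.10 = 0.99 |
| 0.90 | 1.20 | 0.90 × 1.20 = 1.08 |
| 1.00 | 1.10 | 1.00 × 1.10 = 1.10 |
| 0.90 | 0.90 | 0.90 × 0.90 = 0.81 |

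The 10% benefit vanishes when the admission ratio reaches 1/0.90 = 1.11. The last row shows that the distortion can also run the other way.

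**The case against.** **The sentence is narrow.** It sits in the limitation on the injury proxy, and its word for what is controlled has no clear referent. A reader might infer that the protocol vouches for the comparability of beneficiaries and non-beneficiaries in general. It does not say that. The point is therefore anchored on the proxy; the same mechanism reaches the other admission outcomes, but the sentence is not clearly about them.

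**Access is not confined to municipal variables.** A reader might infer that municipal supply is the only access adjustment planned. The text does not support this: the Aim 1 regressions name access to mental health care without a level, and Table 1 lists utilization. The covariate list for Aims 2 and 3 is partly illustrative, and an article may leave definitions to a fuller plan. This weakens any claim that access has been excluded. It does not rescue the reassurance, because adjusting for access cannot remove a difference that BFP itself causes.

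**Admission is the declared outcome.** If BFP changes access and so admissions, that belongs to its total effect on admissions. This stands: an effect estimate is not wrong for that reason. The difficulty begins when admissions are read as illness or impulsivity, as in the mechanism analysis and in the Aim 1 wording about developing mental illness later.

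**Not everything is an admission.** Suicide comes from the mortality system, and violence and self-harm notifications from the notifiable diseases system. This is right, although notifications still depend on contact with services.

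**The ratios are assumed.** They restate their inputs and say nothing about the true size or direction. This stands in full.

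**Conclusion.** The reassurance about the injury proxy is not supported by the analyses described. The BFP match has no access variable, the one adjustment named elsewhere has no measure, and the measured covariates are municipal and concern mental health supply. By the protocol's own account BFP can change access, so part of any difference in admissions may arise after exposure and survive every planned design.

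The size is unknown. The documents give no admission probabilities, and the ratios above only show that a modest change in admission could offset an assumed 10% effect. The conclusion rests on two premises: that BFP affects access, which the protocol expects, and that admissions are read as illness or impulsivity. It does not extend to suicide deaths from the mortality register, nor to estimates presented strictly as effects on admissions. This warrants a correction; it does not invalidate the study.

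**What to change.** 1. Withdraw or narrow the Discussion sentence. State that admission results combine a change in illness or injury with a change in being admitted.
2. Add to the BFP matching list the baseline health care utilization variable from Table 1, measured before BFP receipt, and the municipal supply measures from Aims 2 and 3. Say that this handles pre-existing access differences only; it does not cure a difference caused by BFP.
3. As a sensitivity check for BFP-induced access, run the same designs on a pre-specified set of admissions in the Hospital Information System whose occurrence BFP is not expected to change. Report these beside the main results. Do not divide one by the other as a correction, since nothing in the documents shows that the control admissions carry the same admission ratio as psychiatric or injury admissions.
4. Set the admission results against suicide from the mortality system, and describe the latter as the outcome that does not depend on admission.

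The cost is wording, extra matching variables and one added outcome set from a source already held, with modest extra analysis. The harder part is justifying the negative-control set in advance, because a program with health conditionalities may affect many kinds of admission.

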## Abbreviations

BFP: Bolsa Familia Programme
CadÚnico: Unified Registry for Social Programs
CCT: Conditional Cash Transfer
CIDACS: Center for Data and Knowledge Integration for Health
CNS: National Health Council
DATASUS: Data webpage from the Brazilian Ministry of Health
FIOCRUZ: Oswaldo Cruz Foundation
HDI: Human Development Index
LMIC: Low- and middle-income countries
MS: Microsimulation Models
NIS: Social Identification Number
PSM: Propensity Score Matching
PTSD: Post-Traumatic Stress Disorder
RDD: Regression Discontinuity Design
ROC: Receiver Operating Characteristic
SDG: Sustainable Development Goals
SEM: Structural Equation Modelling
SIH: Hospitalization Information System
SIM: Mortality Information System
SINAN: Notifiable Diseases Information System
UN: United Nations
WHO: World Health Organisation
